#### Sample size and power

The sample size was calculated using Medcalc (Medcalc Software bvba.). This calculation was based on data of the primary outcome measure, obtained in a pilot study of 14 patients. Sample size calculation was performed for the clinically relevant change of 13 points in TFI score. The sample size was calculated for the study to have 80% power to reject the null hypothesis (H_0_). The type I error probability, associated with this test, is 0.05. To achieve the 80% power, 17 patients are needed in each group.

The primary analysis population is the intention-to-treat population. This population includes all randomized patients who provided baseline data, regardless of whether or not they adhere to the complete protocol.

#### Statistics

The primary statistical hypotheses are:

H_0_: Change in TFI-baseline to TFI-6 weeks (treated) = Change in TFI-baseline to TFI-6 weeks (waiting list)

Change in NBQ-baseline to NBQ-6 weeks (treated) = Change in NBQ-baseline to NBQ-6 weeks (waiting list)

The primary outcome is a change in the scores on the TFI and NBQ after 6 weeks. The mean change in TFI and NBQ-baseline and TFI and NBQ 6-week follow-up scores will be calculated.

This mean change in TFI and NBQ scores of the treated group will be compared to the mean change in TFI and NBQ scores of the waiting list group.

A repeated measures ANOVA and post hoc tests will be used to compare the mean changes of the treatment and waiting list population at 6 weeks and secondary at baseline, 12, and 18 weeks follow-up.

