### Outcome measures

The primary outcome measures are the TFI [13] and NBQ [14].

The TFI focuses on eight different domains: the unpleasantness of the tinnitus; reduced sense of control; cognitive interference; sleep disturbance; auditory difficulties attributed to the tinnitus; interference with relaxation; reduction in quality of life; and emotional distress. The test-retest reliability of the TFI is good (r: 0.78). The convergent validity with the Tinnitus Handicap Inventory (r: 0.86) and Visual Analogue Scale (r: 0.75) is good, as well as the discriminant validity with the Beck Depression Inventory-Primary Care (r: 0.56). The clinically relevant reduction was a 13-point reduction.

The pilot study showed that the studied treatment had most influence on the ‘reduced sense of control’ and ‘interference with relaxation’ subscales. Consequently, special attention to these subscales will be paid.

The secondary outcome measures will be the NBQ, a set of different biomechanical and sensorimotor neck parameters and the tinnitus loudness.

The NBQ [14] consists of seven questions on the severity of the neck complaint and its interference with the patient’s wellbeing and professional and daily activities. The test-retest reliability of the NBQ is moderate (ICC: 0.65). The construct validity was acceptable with both the Neck Disability Index (r: 0.50) and the Copenhagen Neck Functional Index (r: 0.44). The effect size was found to be high (Cohen’s d: 1.67), which indicates that the NBQ is highly responsive to changes in cervical spine complaints.

For measuring the biomechanical and sensorimotor neck parameters, the cervical spine mobility will first be investigated in the three cardinal planes.

The range of motion (ROM) is registered using a VICON® measuring device. This device uses the reflection of ultraviolet light on applied markers to perform a 3D movement analysis. The mean absolute error of this measuring device in dynamic conditions is 0.48° (SD 0.05°).

Second, the sensorimotor control of the cervical spine will be measured using the head repositioning accuracy (HRA) to the neutral head position and the continuous linear movement test (CLMT). The HRA measurement will be executed as described by Revel et al. [17] in 1991. The VICON® will be used to register the joint position errors.

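### The primary comparison of TFI and NBQ change at week 6 is not adjusted for baseline, which costs some precision at no benefit, and the named ANOVA leaves open who enters the week-6 comparison

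*Protocol article*

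**What the plan says.** The Statistics section states the null hypotheses as equal change from baseline to week 6 in the treated and waiting-list arms, for TFI and for NBQ. The comparison is then set out: "This mean change in TFI and NBQ scores of the treated group will be compared to the mean change in TFI and NBQ scores" on the waiting list. The tool is a repeated measures ANOVA with post hoc tests, with week 6 as the main time point and baseline, 12 and 18 weeks as secondary. No baseline covariate is named.

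Sample size and power makes intention-to-treat the primary population: "This population includes all randomized patients who provided baseline data, regardless of whether or not they adhere to the complete protocol". The same section gives the inputs to the sample size. On the target difference it says: "Sample size calculation was performed for the clinically relevant change of 13 points in TFI score". Power is set at 80%, and on the error rate it says: "The type I error probability, associated with this test, is 0.05". For the variability it points to the pilot: "This calculation was based on data of the primary outcome measure, obtained in a pilot study of 14 patients". The result is 17 per group. The SD and the sidedness of the test are not given. The Discussion gives a total of 40 patients.

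Outcome measures gives one reliability for each questionnaire: "The test-retest reliability of the TFI is good (r: 0.78") and "The test-retest reliability of the NBQ is moderate (ICC: 0.65").

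**The concern.** A change score subtracts the whole baseline value, which amounts to a regression with the baseline slope held at 1. When baseline and follow-up have equal SDs, the slope that minimises the residual variance equals their correlation, which is below 1. Two things follow.

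- The estimated treatment effect carries noise that ANCOVA would remove, using a baseline score that is collected in any case.
- If one arm happens to start higher, subtracting the full difference over-corrects. The arm with the higher baseline then looks as if it improved more than it did.

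Both effects matter more with 17 to 20 patients per arm than in a large trial.

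There is also an open question about the model. A classical repeated measures ANOVA uses only patients with a score at every visit in the model. If one model covers baseline and weeks 6, 12 and 18, a patient seen at week 6 but not at week 18 would leave the week-6 comparison. Under Study design, the waiting list is treated in the second six weeks, so week 6 is the only treated-versus-untreated contrast. Later attendance should not decide who is in it.

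**Working it through.** **1. The plan's own figure.** The 17 per group cannot be reproduced because the SD is not stated. It can only be back-solved. For a 13-point difference, 80% power and alpha 0.05, 17 per group fits these ranges for the SD of change:

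| Formula | SD of change |
|---|---|
| Two-sample t, two-sided | 12.70 to 13.11 |
| Two-sample normal, two-sided | 13.13 to 13.52 |
| Two-sample normal, one-sided | 14.79 to 15.24 |
| One-sample or paired normal, two-sided | 18.57 to 19.13 |

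I use 13.1 with a two-sided two-sample t test. That gives 80.1% power at 17 per arm, which agrees with the plan.

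**2. Variance of ANCOVA relative to the change score.** Let s be the common SD at both visits and r the correlation between them.

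- Change score: 2(1 − r)s²
- ANCOVA residual: (1 − r²)s²
- Ratio: (1 − r²) / [2(1 − r)] = (1 + r)/2

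The article gives no baseline to week-6 correlation, so its test-retest values serve as a proxy (an assumption).

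- TFI: (1 + 0.78)/2 = 0.89, so change scores need 1/0.89 = 1.12 times as many patients.
- NBQ: (1 + 0.65)/2 = 0.825, so 1/0.825 = 1.21 times as many.

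The true correlation may be lower, because entry is restricted on both scales and treatment may weaken it. At r = 0.5 the ratio is 0.75.

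**3. TFI power** (noncentral t, two-sided, 13 points, SD of change 13.1; ANCOVA SD = 13.1 × √ratio)

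| Analysis | SD used | 17 per arm | 20 per arm |
|---|---|---|---|
| Change score | 13.1 | 80% | 86% |
| ANCOVA, r = 0.78 | 12.4 | 84% | 90% |
| ANCOVA, r = 0.5 | 11.3 | 90% | 94% |

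Estimating the slope costs a little. The expected variance inflation is 1 + 1/(N − 4), which is 1 + 1/30 = 1.033 for N = 34. That takes about one point off the ANCOVA rows. Over SDs from 12.7 to 18.8 the gain at r = 0.78 and 17 per arm stays at 4 to 5 points (82% to 87% at 12.7, 50% to 54% at 18.8). No NBQ power can be given, because the article states no NBQ target difference.

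**4. Chance imbalance.** With 17 per arm, the standard error of the baseline difference is √(2/17) = 0.34 s. With SD of change 13.1, s = 13.1/√(2(1 − r)), which is 19.7 at r = 0.78 and 13.1 at r = 0.5. A one-standard-error imbalance is then 6.8 or 4.5 TFI points. The change score over-corrects by (1 − r) times that: 0.22 × 6.8 = 1.5 points, or 0.5 × 4.5 = 2.2 points, against a 13-point target.

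**5. Complete-case loss, only if all four visits are modelled classically.** Assume each of the three follow-up visits is missed independently at rate m (not in the article). The complete fraction is (1 − m)³; a week-6-only comparison keeps (1 − m). Power uses change scores with SD 13.1.

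| m | Start per arm | Four visits: n, power | Week 6 only: n, power |
|---|---|---|---|
| 5% | 17 | 14.6, 73% | 16.2, 78% |
| 5% | 20 | 17.1, 80% | 19.0, 85% |
| 10% | 17 | 12.4, 66% | 15.3, 76% |
| 10% | 20 | 14.6, 73% | 18.0, 82% |

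**The case against.** The best defence has four parts.

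- **The change score is a legitimate estimator.** It uses the baseline, is unbiased under randomisation, and matches a sample size built on a 13-point change. This stands. The matter is one of efficiency, and a reader who inferred that the baseline is thrown away or that the primary result is biased would go too far.
- **The article does not say that anyone is dropped.** A reader might infer that every patient with a missed visit is excluded and that this contradicts the intention-to-treat definition. The text does not support that. It contains no complete-case rule, does not say whether the week-6 test uses two or four time points, and may leave missing data to an analysis plan that is not shown. If only baseline and week 6 enter the test, a missed week 12 or 18 removes nobody. This stands too: what remains is conditional.
- **Power at the stated recruitment is better than 17 per arm suggests.** With 40 patients, 5% missed per visit still leaves about 80% even under the four-visit complete-case form. At 10% it does not (73%).
- **The gain at the cited correlations is modest and rests on assumptions.** True: about 4 points for TFI. But the ratio (1 + r)/2 is below 1 for any r below 1, so with equal SDs the direction does not depend on the proxy; at r close to 1 the cost of estimating the slope offsets the small gain.

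**Conclusion.** The point holds as a matter of precision and of specification. The article itself fixes an unadjusted change-score comparison, so this is a choice made rather than a detail left out. At the cited reliabilities the ANCOVA variance is 0.89 (TFI) and 0.825 (NBQ) of the change-score variance. For TFI that means about 80% to 84% power at 17 per arm and 86% to 90% at 20 per arm, or about 90% at 17 per arm if r is 0.5. This rests on equal SDs at both visits, reliability standing in for the baseline to week-6 correlation, a two-sided test, and an SD of change of about 13.1; none of these is stated.

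The link to intention-to-treat is conditional. A classical four-visit repeated measures ANOVA would not deliver the stated population, and the article does not say whether that is what will be run. It is a gap in fit between the named method and the population, not a demonstrated contradiction.

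**What to change.** Replace the primary analysis in the Statistics section with one of the following, fixed before the data are analysed:

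- an ANCOVA of the week-6 score on arm, with the baseline score as covariate; or
- a likelihood-based linear mixed model adjusted for baseline, with the arm contrast at week 6 named as primary and weeks 12 and 18 as secondary.

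Use the same model for TFI and NBQ. State that a missed visit at week 12 or 18 does not remove a patient from the week-6 comparison. The ANCOVA alone still needs a week-6 score, so patients without one need a rule, here or in the analysis plan. The mixed model can use their later scores under a missing-at-random assumption.

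The cost is a few lines of text. No extra patients, visits or data are needed, and the 13-point target can stay as it is, because under randomisation the adjusted week-6 difference and the difference in mean change estimate the same treatment effect.

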**Methods and design:**

This study is designed as a randomized controlled trial with delayed treatment design. Patients with severe subjective tinnitus (Tinnitus Functional Index (TFI) between 25 and 90 points), in combination with neck complaints (Neck Bournemouth Questionnaire (NBQ) >14 points) will be recruited from the University Hospital of Antwerp.

Patients suffering from tinnitus with clear otological etiologies, severe depression, traumatic cervical spine injury, tumors, cervical spine surgery, or conditions in which physical therapy is contra-indicated, will be excluded.

After screening for eligibility, baseline data such as TFI, NBQ, and a set of cervical biomechanical and sensorimotor tests will be collected.

Patients are randomized in an immediate therapy group and in a group with a delayed start of therapy by 6 weeks.

Patients will receive physical therapy with a maximum of 12 sessions of 30 min for a 6-week program. Data from the TFI and NBQ will be collected at baseline (week 0), at the start of therapy (weeks 0 or 6), at the end of therapy (weeks 6 or 12), 6 weeks after therapy (weeks 12 or 18), and 3 months after therapy (weeks 18 or 24). Secondary outcome measures will be collected at baseline and 6 weeks after the therapy (weeks 12 or 18), as the maximal therapy effect on the cervical spine dysfunctions is expected at that moment.

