### Study design

This study is designed as an RCT to evaluate the effectiveness of a standardized cervical spine treatment on tinnitus and neck-related parameters in patients suffering from CST. A delayed treatment design (Figure 1) will be used to create a waiting list to obtain the data for the control group [16]. At baseline, patients are randomly assigned by the responsible researcher to receive immediate treatment or to the waiting list. In part 1, the immediate treatment group receives the cervical spine treatment for 6 weeks. In part 2, the patients on the waiting list receive cervical spine treatment for the next 6 weeks. The immediate treatment group now enters a 6-week follow-up period. In part 3, all patients enter a follow-up period which ends 12 weeks after the last treatment session.

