The continuous linear movement test (CLMT), as described by Sjolander et al. [18], will be used to objectify the movement speed, acceleration, and Jerk index using the VICON® data. Special attention will be paid to the movement speed and acceleration, as these parameters have proven to have good test-retest reliability [19].

Third, a set of tests will be executed to objectify the impairments in cervical spine mobility and muscle function. This set of tests includes a manual investigation of the cervical spine, tenderness of trigger points, and a strength and endurance test of the deep neck flexor muscles [20]. The manual investigation consists of a manual rotation test and adapted Spurling test [15], and a flexion rotation test evaluating the upper cervical spine rotation mobility [21]. The tenderness of 16 trigger points, is investigated by applying manual pressure [22]. The strength and endurance of the deep neck flexor muscles is objectified using the craniocervical flexion test [20].

All outcome measures will be documented at baseline and at 12 weeks. The primary outcome measures will additionally be documented at 6 and 18 weeks.

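### The secondary treatment-versus-waiting-list comparisons at 12 and 18 weeks compare immediate with delayed start, because the waiting-list arm has been treated by then; they cannot show benefit or durability

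*Protocol article*

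**What the plan says.** The primary hypotheses in the Statistics section concern week 6. For the TFI the null is "Change in TFI-baseline to TFI-6 weeks (treated) = Change in TFI-baseline to TFI-6 weeks (waiting list"), and the NBQ has a matching one. The same section then assigns the analysis to a repeated measures ANOVA with post hoc tests, used to "compare the mean changes of the treatment and waiting list population at 6 weeks and secondary at baseline, 12, and 18 weeks follow-up".

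The Study design section says what happens after week 6: "In part 2, the patients on the waiting list receive cervical spine treatment for the next 6 weeks". Of the other arm it says: "The immediate treatment group now enters a 6-week follow-up period".

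The Abstract (Methods and design) schedules TFI and NBQ by time since therapy, with two calendar weeks for each visit. Therapy finishes at week 6 in the immediate arm and week 12 in the delayed arm, and the later visits are given as "6 weeks after therapy (weeks 12 or 18), and 3 months after therapy (weeks 18 or 24"). The Outcome measures section gives single week numbers. It places all outcomes at baseline and 12 weeks, and adds: "The primary outcome measures will additionally be documented at 6 and 18 weeks".

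**The concern.** The Statistics section names the two populations at 12 and 18 weeks as it does at week 6, as treatment and waiting list. At week 6 that label is right. Later it is not, because the waiting-list patients have by then had the same course of therapy. The section neither says this nor aligns the later visits to time since therapy.

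The follow-up visits are there to show whether benefit lasts. If they are analysed and labelled as written, a therapy whose benefit lasts completely gives no between-arm difference at 12 and 18 weeks. A reader who takes the label at face value would see an effect at week 6 that has gone by week 12.

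**Working it through.** **1. Where each arm stands at each calendar week** (Study design; Abstract, Methods and design)

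| Calendar week | Immediate arm | Waiting-list arm | What the contrast compares |
|---|---|---|---|
| 0 | before therapy | before therapy | baseline |
| 6 | end of therapy | untreated | treated vs untreated |
| 12 | 6 weeks after therapy | end of therapy | treated vs treated, 6 weeks apart |
| 18 | 12 weeks after therapy | 6 weeks after therapy | treated vs treated, 6 weeks apart |

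**2. The other reading of the weeks.** Suppose 12 and 18 weeks run from the start of therapy, so that the delayed arm is seen at calendar weeks 18 and 24. Both arms are then 6 and 12 weeks past therapy, and the contrast is again treated versus treated. The week-6 waiting-list value must be calendar time on any reading, since that arm is still waiting. The conclusion does not depend on the choice.

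**3. Size under a fully lasting benefit.** Take the 13-point TFI change from Sample size and power. Mean changes are 0, −13, −13, −13 in the immediate arm and 0, 0, −13, −13 in the waiting-list arm. The differences in size are 0, 13, 0, 0. A test with no true difference rejects at its alpha, 5%. Simulation agrees: 4.6% to 5.7% at week 12 (17 and 20 per arm, SD of change 13.3, 3,000 runs per setting) and 4.5% to 4.9% at week 18 (17 per arm, SD 13.1, 4,000 runs per setting).

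**4. The plan's own figure of 17 per group.** The article gives 13 points, 80% power and alpha 0.05, but no SD, so 17 can only be solved backwards. Using n = 2(1.960 + 0.842)² × SD² / 13², two-sided, 17 per group follows for an SD of change between 13.13 and 13.52. A t-based calculation gives 12.70 to 13.11. A one-sided test would give 14.79 to 15.24. I use 13.3 as an assumption.

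**5. The week-6 contrast alone.** Standard error = 13.3 × √(2/17) = 4.56, and 13 / 4.56 = 2.85. Power ≈ Φ(2.85 − 1.96) = Φ(0.89) ≈ 0.81. In the simulated four-visit data the week-6 contrast averaged 12.95 to 13.16 points, with power 0.79 to 0.80 at 17 per arm and 0.84 to 0.86 at 20 per arm. Including the later visits does not shrink it.

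**6. What other decision rules would do.** The text states neither of these. Compound symmetry is assumed, with correlation ρ = 0.5 or 0.78 (the second is the TFI test-retest value in Outcome measures).

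- *Group main effect.* The difference averages (0 + 13 + 0 + 0) / 4 = 3.25 points. The per-visit SD is 13.3 / √(2(1 − ρ)), and the SD of a four-visit mean is that value × √((1 + 3ρ)/4).
  - ρ = 0.5: 13.3 × √0.625 = 10.5; standard error 3.61; ratio 0.90; power about 15%.
  - ρ = 0.78: 20.05 × √0.835 = 18.3; standard error 6.28; ratio 0.52; power about 8%.
  - Simulation gives 8% to 15% at 17 per arm and 10% to 17% at 20 per arm.
- *Week-6 test only after a significant group-by-time interaction.* Simulated power is 73% to 75% at 17 per arm and 81% to 82% at 20 per arm.

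**The case against.** The strongest reply is that the primary analysis is sound. The hypotheses are fixed at week 6, the later visits are called secondary, and the article says openly that the waiting list is treated after 6 weeks. All of this stands, and it limits the point to the secondary comparisons.

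A reader might go further and infer that pooling four visits in one ANOVA dilutes the week-6 contrast, or that the week-6 test loses its stated power. The document does not support that. The contrast keeps about 13 points and about 80% power. A loss needs a rule that is not written: the group main effect as the deciding test, an interaction gate, or a Bonferroni split over three post-baseline visits (about 64% at 17 per arm with SD 13.1). The deciding term and any gate are commonly left to the analysis plan, so silence on them in an article is not itself an error. Moreover, the Discussion speaks of 40 patients, or 20 per arm, where even the gated test stays above 80%.

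It is also fair to say that the 12- and 18-week comparisons remain randomised. They validly estimate the effect of starting now rather than 6 weeks later, and catch-up by the delayed arm is informative. They need not be deleted if they are labelled correctly.

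Finally, a reader might expect follow-up to favour the waiting list. If the benefit halved by 6 weeks after therapy, calendar week 12 would do so by 13 − 6.5 = 6.5 points. That needs a decay the article does not give, and the calendar reading of the weeks. I do not rely on it.

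**Conclusion.** The point holds for the secondary comparisons at 12 and 18 weeks. On either reading of the weeks both arms have been treated, so the contrast is immediate versus delayed start. A fully lasting 13-point benefit gives a true difference of 0 and a rejection rate of about 5%. The comparison as labelled can show neither efficacy nor durability. This follows from the schedule and needs no SD or correlation.

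The primary week-6 contrast is intact. All power figures here rest on an SD that is back-solved rather than stated, on a two-sided test, and on assumed correlations. The losses under a main-effect test or an interaction gate are conditional risks that one sentence would close off. Severity: should-fix.

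**What to change.** Three changes to the Statistics section:

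1. State that the between-arm contrast in change from baseline to week 6 alone tests each primary hypothesis (TFI and NBQ), with no omnibus test as a gate.
2. Do not present the 12- and 18-week comparisons as treatment versus waiting list. Drop them, or label them immediate versus delayed start and say whether weeks run from randomisation or from the start of therapy.
3. Report durability as within-patient change aligned to time since therapy, labelled uncontrolled:

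| | Pre-therapy | End of therapy | +6 weeks | +12 weeks |
|---|---|---|---|---|
| Immediate arm | week 0 | week 6 | week 12 | week 18 |
| Delayed arm | week 6 | week 12 | week 18 | week 24 |

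The Abstract already schedules these visits, and Study design runs follow-up to 12 weeks after the last session. Outcome measures stops at 18 weeks, so its wording should be brought into line with the week-24 visit in the delayed arm.

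The cost is wording only, with no added patients or visits. The trial forgoes a randomised treated-versus-untreated claim beyond week 6, which the delayed-treatment design does not support in any case.
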